## Background

Multiple sclerosis (MS), a chronic inflammatory disease of the central nervous system, is the most common disabling neurologic disorder of young adults. The causes of MS remain unknown, but it is widely believed that there is interplay between genetic and environmental factors [1]. Evidence for the role of the environment in the development of MS is supported by a strong correlation between MS incidence/prevalence and increased latitude and lower levels of sun exposure, suggesting an association with vitamin D production [2-4]. Individuals who emigrate before the age of 15 years from an area of high MS prevalence to one of low prevalence, acquire the lower risk of MS in their new country of residence. Migration studies provide perhaps the strongest support for the role of environmental factor(s) in this disease [5,6].

People living at high latitudes are generally deficient in vitamin D, as measured by serum 25-hydroxyvitamin D (25(OH)D) levels [7,8]. In one study, mean winter 25(OH)D levels in healthy control subjects in Ireland were 36.4 nmol/l, and more patients with MS had vitamin D deficiency (serum 25(OH)D levels less than 25 nmol/l) compared with control subjects [9]. Patients have lower serum vitamin D levels during MS relapses, and also have blunted parathyroid hormone responses [10,11]. In 267 Dutch patients with relapsing remitting multiple sclerosis (RRMS), higher vitamin D levels were associated with an increased chance of remaining relapse-free [11]. In 134 North American patients with RRMS or clinically isolated syndrome (CIS) of pediatric onset, the strongest predictor of further relapse was the baseline serum vitamin D level [12]. In a prospective Australian study of 145 patients with RRMS, each increase of 10 nmol/l in baseline serum vitamin D level was associated with a 12% reduction in the risk of a further relapse [13]. Vitamin D deficiency may increase susceptibility to MS even *in utero*; higher maternal vitamin D intake during pregnancy was associated with a 38% lower risk of MS in offspring [14], and maternal vitamin D levels greater than 75 nmol/l were associated with a 61% reduced risk of MS in children [15]. Month of birth studies showing an increased MS incidence in those with spring versus autumn births also provide evidence of the role of maternal vitamin D [16].

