The potential therapeutic effect of vitamin D supplementation was first suggested by Goldberg in 1986 [17]. Dosing studies in healthy volunteers have shown that supplementation with vitamin D 10,000 IU daily results in an increase in serum 25(OH)D levels of 150 nmol/l over a 12 week period [18]. A Canadian phase I/II open-label, randomized, placebo-controlled trial (RCT) of 49 patients with RRMS who were randomized to placebo or escalating doses of vitamin D over a 52 week period showed a trend toward relapse reduction in the actively treated group [19]. This study was primarily aimed at establishing the safety and tolerability of high-dose vitamin D supplementation; the mean vitamin D dose was 14,000 IU per day, and there were no adverse events or hypercalcamia despite maximum mean vitamin D levels of 413 nmol/l being achieved. The results from this phase II trial [19], and from dosing [18] and observational studies [12,13], suggest that pharmacologic doses of vitamin D of up to 10,000 IU/day are safe, and may reduce the risk of relapse by a factor superior to the 30% reduction reported from the pivotal trials of interferons in RRMS [20,21].

Vitamin D modulates both the innate and adaptive immune systems [22]. The active metabolite, 1,25 (OH) vitamin D, primarily mediates its effects through the intracellular vitamin D receptor (VDR) [23], which is present in monocytes, dendritic cells, B-cells, and CD4+ T-cells [11,22]. Activation of VDR alters transcription, proliferation, and differentiation of immune cells [23], and modulates immune response both indirectly, by reducing the activation of pro-inflammatory T-cells by antigen-presenting cells [24], and directly, by inhibiting T-cell and B-cell proliferation [22,25]. This results in a T-helper (Th) 2-cell driven anti-inflammatory state [11,22,26].

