#### Exclusion criteria

Exclusion criteria both for patients with CIS and for healthy control participants include: no history or evidence of hypercalcemia, renal impairment, vitamin D intolerance, parathyroid dysfunction, sarcoidosis, prior or current treatment with thiazide diuretics, or vitamin D supplementation of greater than 1,000 IU/day. Exclusion criteria for patients with CIS include: 1) if their symptoms might be explained by another diagnosis other than MS; 2) occurrence of an exacerbation less than 6 weeks prior to study entry; 3) previous treatment with β-interferons or glatiramer acetate in the 3 months before study entry, previous treatment with steroids in the 4 weeks before study entry, or any previous treatment with mitoxantrone or other immunosuppressant; and d) concurrent enrolment in any other clinical trial investigating DMT in CIS.

All female patients and healthy controls will be advised not to become pregnant for the duration of the study, and if sexually active to use effective contraception for the duration of the study and for 3 months after.

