### Randomization

Patients with CIS and healthy control participants who fulfill the inclusion criteria will be enrolled in the study after providing informed consent at the screening visit. At the baseline visit, study participants who remain eligible will be assigned a number in ascending order: 1 to 45 for the CIS group and 1 to 39 for controls. The CIS group will be denoted by an X before this number, and the controls a Y. These numbers were randomized using the software program GraphPad [30] by the hospital pharmacist. The healthy control participants and patients with CIS will be randomized separately to maintain equal numbers in the three treatment arms of both these study groups.

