#### Placebo therapy

A placebo oil, not containing vitamin D but identical to the active principle in all other respects, will be used.

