### Statistical methods

All analyses assume a two-sided test of hypothesis with an overall α level of 0.05. Immunologic endpoints and *post hoc* analyses, which will include the 16 and 24 week endpoints, are considered exploratory, and will not be adjusted for multiple comparisons. Descriptive statistics will be presented as mean ± SD. Non-parametric tests will be used to compare characteristics between treatment groups. For outcomes, the sign/sign rank test will be used to evaluate continuous outcomes. McNemar testing will be used to categorize categorical and binary outcomes. For non-parametric testing on unpaired continuous data, the Wilcoxon rank sum test will be used. All outcomes will be adjusted for baseline serum 25(OH)D levels, and for mean serum levels achieved at weeks 16 and 24.

Missing data will be imputed as the mean of the preceding and following measurements. Only patients completing at least 4 months of full participation in the study or experiencing a relapse at any time in the study will be included in the final analysis. Non-adherent participants, defined as those with an increase in serum level of 25(OH)D of less than 50 nmol/l from baseline, will be excluded from the final analysis.

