## Discussion

Supplemental vitamin D appears to have potential as a therapeutic agent for MS; what is less clear is the optimal dose of vitamin D needed to effect change within the immune system. Our study is designed to address this question, and to add to the growing evidence of the safety and tolerability of high-dose vitamin D supplementation. As this is a phase II randomized, placebo-controlled trial with two distinct study groups and is adequately powered to meet the primary endpoint, it should be considered a high-quality trial aiming to provide class II evidence of the primary endpoint.

Existing guidelines on vitamin D supplementation are conservative, and refer mainly to bone health [33], with 4,000 IU considered the upper limit of tolerability, despite the fact that sun exposure can provide an adult with up to 20,000 IU per day [34]. Older adults are now advised to sustain 25(OH) D concentrations of greater than 75 nmol/l for optimal bone health and, in order to achieve that, they need to consume approximately 4,000 IU/day of vitamin D [18,35]. Levels greater than 100 nmol/l are needed to ensure that patients are receiving adequate immunomodulating doses of vitamin D. Based on previous dosing studies [18], the maximum serum 25(OH)D level expected with a daily dose of 10,000 IU is approximately 250 nmol/l, making both treatment doses safe and tolerable.

The availability of DMT and the earlier recognition and diagnosis of MS have a significant effect on trial design for the evaluation of new drugs, and this also raises ethical concerns. Most would feel that placebo-controlled studies of the RRMS population are unethical. This results in the need for large multicenter trials to achieve adequate numbers to power the study over longer time periods to assess for clinical endpoints. Thus, costs are generally prohibitive and really limits these studies to large pharmaceutical companies.

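### The 50 nmol/l serum-rise rule for adherence excludes almost the whole placebo arm as written, and selects unevenly between doses if limited to active arms

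*Protocol article*

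**What the plan says.** The Statistical methods section of the protocol article defines adherence by a blood level alone: "Non-adherent participants, defined as those with an increase in serum level of 25(OH)D of less than 50 nmol/l from baseline, will be excluded". The exclusion applies to the final analysis. The sentence applies to participants in general, names no treatment arm, and is not labelled as a per-protocol or sensitivity rule. No other analysis set is described beside it.

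Under Placebo therapy the article states: "A placebo oil, not containing vitamin D but identical to the active principle in all other respects, will be used". Under Study endpoints, the primary endpoint and the secondary MRI, relapse and disease-activity endpoints each compare the two vitamin D doses with placebo.

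On the expected rise, the Background reports that "supplementation with vitamin D 10,000 IU daily results in an increase in serum 25(OH)D levels of 150 nmol/l over a 12 week period". The article gives no corresponding figure for 5,000 IU and no SD for the change. The exclusion criteria bar "vitamin D supplementation of greater than 1,000 IU/day", so smaller supplements are allowed, and they set no upper limit on baseline 25(OH)D.

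**The concern.** The rule uses a pharmacological response as its test of adherence. In the placebo arm, full adherence should produce no rise, so the rule takes out the comparator on which the endpoints depend.

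In the active arms, the rise depends on dose, baseline level and season as well as on whether the oil was taken. A fully adherent person on the lower dose, or one who starts high or enters in summer, can rise by less than 50 nmol/l and be removed. Applied only to active arms, the rule would compare biochemical responders with an unselected placebo group and would select more strongly at 5,000 IU than at 10,000 IU. Either way, the groups analysed are no longer the groups randomised.

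**Working it through.** **Planned numbers.** Participants are "randomized separately to maintain equal numbers in the three treatment arms" of each study group, which gives 39/3 = 13 controls and 45/3 = 15 CIS patients per arm. The Sample size section asks for at least 10 per group and allows for 20% and 30% drop-out. These figures reproduce: 10/0.80 = 12.5, rounded up to 13, times 3 = 39; and 10/0.70 = 14.3, rounded up to 15, times 3 = 45. After drop-out, 13 × 0.80 = 10.4 and 15 × 0.70 = 10.5 remain per arm, so nothing is left over for a further exclusion.

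**Placebo arm.** With a normally distributed change, the share retained is P(rise ≥ 50) = 1 − Φ((50 − mean)/SD). Means and SDs are assumptions. A positive mean stands for season or permitted supplements. Counts are before drop-out.

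| Mean, SD (nmol/l) | Share retained | Of 13 controls | Of 15 CIS | Of 28 |
|---|---|---|---|---|
| 0, 15 | 0.04% | 0.01 | 0.01 | 0.01 |
| 0, 20 | 0.6% | 0.08 | 0.09 | 0.17 |
| 0, 25 | 2.3% | 0.30 | 0.34 | 0.64 |
| 20, 20 | 6.7% | 0.87 | 1.0 | 1.9 |
| 30, 20 | 15.9% | 2.1 | 2.4 | 4.4 |
| 30, 30 | 25.3% | 3.3 | 3.8 | 7.1 |

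Even the most generous row leaves 3 or 4 per population, and they are selected for large rises that the trial oil did not cause.

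**What that does to a comparison.** Take the anti-CD3 IL-17 figures from the Sample size section (44.5, SD 44.3), 10 active participants, and power ≈ Φ(44.5/(44.3 × √(1/10 + 1/n)) − 1.96), with n on placebo:

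- n = 10: 0.61
- n = 2: 0.25
- n = 1: 0.16

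With 1 placebo participant against 10 active, the smallest possible two-sided rank-sum p-value is 2/11 = 0.18, so significance at 5% cannot be reached.

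**Active arms.** The share excluded is P(rise < 50) = Φ((50 − mean)/SD). For 10,000 IU the mean is the article's 150. For 5,000 IU, half of that (75) is assumed, with 60 and 90 to show sensitivity.

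| Arm, mean rise | SD 15 | SD 20 | SD 25 | SD 30 | SD 40 |
|---|---|---|---|---|---|
| 5,000 IU, 60 | 25% | 31% | 35% | 37% | 40% |
| 5,000 IU, 75 | 5% | 11% | 16% | 20% | 27% |
| 5,000 IU, 90 | 0.4% | 2% | 6% | 9% | 16% |
| 10,000 IU, 150 | <0.1% | <0.1% | <0.1% | <0.1% | 0.6% |

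At mean 75 and SD 20 to 40, the 5,000 IU arm after planned drop-out falls to between 10.4 × (1 − 0.266) = 7.6 and 10.5 × (1 − 0.106) = 9.4, below the required 10.

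**A rough lower figure.** The Background reports that "mean winter 25(OH)D levels in healthy control subjects in Ireland were 36.4 nmol/l". The Discussion says older adults are advised to "sustain 25(OH) D concentrations of greater than 75 nmol/l" and that for this "they need to consume approximately 4,000 IU/day of vitamin D". Scaling in proportion gives (75 − 36.4) × 5/4 = 48 nmol/l at 5,000 IU, at which 52% to 55% would be excluded for SD 40 down to 15. This mixes two populations and treats a minimum level as a mean, so it shows only how sensitive the answer is.

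**The case against.** The strongest reply is that the rule was plainly meant for the vitamin D arms. A rise in 25(OH)D can only verify intake of active oil, and the code is opened at database lock, so the rule could then be applied to those arms alone. That may be the intent. But the text does not say so, and the reply turns a rule that removes the comparator into one that selects on one side after randomisation.

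Other points stand in part:

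- The loss at 5,000 IU depends on assumed means and SDs. At mean 75 and SD 15 it is only 5%. The Background also expects 5,000 to 10,000 IU to take deficient patients above 100 nmol/l. From below 25 that is a rise of more than 75, so the 48 nmol/l figure should carry little weight.
- How often a high baseline would hold the rise below 50 is not shown, and the article's Irish winter mean is low.
- No listed endpoint compares 5,000 with 10,000 IU directly. Still, the trial is described as dose-ranging and the Discussion poses the question of the optimal dose, so unequal selection distorts what a reader would infer from the two contrasts with placebo.
- In an exploratory mechanistic trial, an analysis of people with verified exposure can be informative. That supports a labelled supplementary analysis. It does not support using the rule to define the only final analysis described.

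**Conclusion.** The concern holds: the rule is wrong as written and must be changed. That the placebo arm fails the definition follows from the wording and the composition of the placebo, and needs no assumed SD. The number retained does rest on assumptions: fewer than 1 of 28 with no drift and SD 15 to 25, and about 4 of 28 with a drift of 30 nmol/l and SD 20.

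Under the active-only reading, the imbalance between doses is about 11% to 27% against under 1%, given a mean rise of 75 at 5,000 IU and SD 20 to 40. The direction is secure as long as the lower dose gives the smaller rise and the spread is similar. The size is uncertain.

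**What to change.** Delete the serum-rise exclusion from the final analysis and state that the main analysis includes all randomised participants in the arm to which they were assigned. The neighbouring sentence that limits the final analysis to those with at least 4 months of participation or a relapse must be brought into line with this.

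Use the rise in 25(OH)D descriptively by arm, or in a secondary exposure-response analysis labelled as such. If a per-protocol sensitivity analysis is wanted, define adherence by a measure that works identically in all three arms, for example the volume left in returned bottles. This part is optional. The article describes no bottle return, and recruitment has begun, so it would need a new procedure.

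The essential change is to text and needs no extra participants. The price is some dilution of the effect estimates by true non-adherence. In return, placebo keeps its planned 10.4 and 10.5 evaluable participants per population.

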## Discussion

Supplemental vitamin D appears to have potential as a therapeutic agent for MS; what is less clear is the optimal dose of vitamin D needed to effect change within the immune system. Our study is designed to address this question, and to add to the growing evidence of the safety and tolerability of high-dose vitamin D supplementation. As this is a phase II randomized, placebo-controlled trial with two distinct study groups and is adequately powered to meet the primary endpoint, it should be considered a high-quality trial aiming to provide class II evidence of the primary endpoint.

Existing guidelines on vitamin D supplementation are conservative, and refer mainly to bone health [33], with 4,000 IU considered the upper limit of tolerability, despite the fact that sun exposure can provide an adult with up to 20,000 IU per day [34]. Older adults are now advised to sustain 25(OH) D concentrations of greater than 75 nmol/l for optimal bone health and, in order to achieve that, they need to consume approximately 4,000 IU/day of vitamin D [18,35]. Levels greater than 100 nmol/l are needed to ensure that patients are receiving adequate immunomodulating doses of vitamin D. Based on previous dosing studies [18], the maximum serum 25(OH)D level expected with a daily dose of 10,000 IU is approximately 250 nmol/l, making both treatment doses safe and tolerable.

The availability of DMT and the earlier recognition and diagnosis of MS have a significant effect on trial design for the evaluation of new drugs, and this also raises ethical concerns. Most would feel that placebo-controlled studies of the RRMS population are unethical. This results in the need for large multicenter trials to achieve adequate numbers to power the study over longer time periods to assess for clinical endpoints. Thus, costs are generally prohibitive and really limits these studies to large pharmaceutical companies.

In Ireland, the UK, Australia, and New Zealand, patients with CIS are treated conservatively until there is evidence, on clinical or MRI grounds, of dissemination in time. Patients with CIS form a distinct population with a well-established natural history, who are not exposed to immunomodulatory therapy. Given the standard practice in Ireland, there is no ethical concern with regard to watchful withholding of treatment. Should patients convert to RRMS during the trial, they will be offered standard DMT. This study should add to the growing evidence of the immunomodulatory effects of high-dose supplemental vitamin D in demyelinating disease. We hope to show that vitamin D is a safe and effective therapy for patients with CIS.

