# Dose-related effects of vitamin D on immune responses in patients with clinically isolated syndrome and healthy control participants: study protocol for an exploratory randomized double- blind placebo-controlled trial

**DOI:** 10.1186/1745-6215-14-272

**Published:** 2013-08-27

**Keywords:** Vitamin D, Clinically isolated syndrome, Multiple sclerosis, Immunomodulation, Cholecalciferol, Clinical trial

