## Methods/Design

### Trial design

This is a single-center investigator-led, phase II, exploratory, double-blind, dose-ranging, randomized, placebo-controlled trial to assess the immune responses to two doses of vitamin D in patients with CIS and in healthy control participants. Recruitment commenced in November 2012. In total, 45 patients with CIS and 39 healthy control participants will be enrolled and randomized to one of three arms, placebo oil or vitamin D oil (Vigantol®; Merck Serono, Darmstadt, Germany) at a dose of 5,000 IU or 10,000 IU, all of which will be taken orally for a period of 24 weeks.

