### Study endpoints

The primary endpoint is the effect of oral vitamin D at 5,000 and 10,000 IU/day compared with placebo on the frequency of CD4 T-cell subsets and cytokine responses in peripheral blood mononuclear cells in patients with CIS and in healthy control participants at weeks 16 and 24 compared with baseline.

Secondary endpoints include: the following. 1) In the patients with CIS having MRI brain scans at baseline and week 24, the number of new and enlarging T2 lesions and gadolinium-enhancing lesions at week 24 compared with baseline in patients receiving oral vitamin D at 5000 IU and 10,000 IU/ day compared with placebo, 2) In the patients with CIS, the effects of oral vitamin D at 5,000 and 10,000 IU/day compared with placebo on relapse occurrence, calculated as the annualized relapse rate (ARR), the percentage of patients who are relapse-free, and time to first relapse. 3) The effects of oral vitamin D at 5,000 and 10,000 IU/day compared with placebo on the percentage of treated patients with CIS who are free from any evidence of disease (clinical and MRI) activity.

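### The trial is presented as addressing dose and the optimal dose, but every specified between-arm comparison is with placebo and none is between 5,000 and 10,000 IU

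*Protocol article*

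**What the plan says.** Three places in the protocol article set dose as the question.

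- The title: "Dose-related effects of vitamin D on immune responses in patients with clinically isolated syndrome and healthy control participants".
- Trial design: "exploratory, double-blind, dose-ranging, randomized, placebo-controlled trial to assess the immune responses to two doses of vitamin D".
- Discussion: "what is less clear is the optimal dose of vitamin D needed to effect change within the immune system", followed by "Our study is designed to address this question".

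The comparisons are fixed elsewhere. Study endpoints states: "The primary endpoint is the effect of oral vitamin D at 5,000 and 10,000 IU/day compared with placebo". The three secondary endpoints (MRI lesions, relapse, freedom from disease activity) are also set against placebo, as are the comparisons in the abstract.

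Statistical methods names sign or signed-rank tests for continuous outcomes, McNemar's test for categorical ones, and, for independent groups: "For non-parametric testing on unpaired continuous data, the Wilcoxon rank sum test will be used". It does not say which arms that test compares. It also adjusts all outcomes for baseline 25(OH)D and for the mean level reached at weeks 16 and 24.

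Sample size rests on changes seen in four healthy participants who took 5,000 to 10,000 IU/day. It does not split them by dose and assumes no difference between doses.

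**The concern.** A question about dose needs a contrast that involves the two doses. Here the endpoints supply 5,000 IU against placebo and 10,000 IU against placebo, and nothing is specified that links them. Whoever writes the dose conclusion then has only two small placebo comparisons to set next to each other. If one is significant and the other is not, it is easy to read this as a dose effect, although the difference between the doses has not been tested.

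The planned adjustment for achieved 25(OH)D makes this worse. Dose acts largely through that level, so conditioning on it would take out much of any real difference between the doses.

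What is at stake is the dose claim. The placebo comparisons keep their own meaning.

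**Working it through.** **1. The plan's own figure.** Sample size asks for at least 10 per group. A two-sided paired t-test at 5% with 80% power gives:

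- IL-17 after anti-CD3 (44.5 ± 44.3): 9.87, so 10, as stated.
- IFN-γ after PPD (1860 ± 1835): 9.73, so 10, as stated.
- Th1 cells (4.3 ± 6.3): 18.86, so 19, as stated.
- Drop-out: 10/(1 − 0.20) = 12.5, so 13 per arm and 3 × 13 = 39 controls; 10/(1 − 0.30) = 14.3, so 15 per arm and 3 × 15 = 45 patients. Both totals match.

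The formula does not reproduce every endpoint (Th17 gives 10, not 5), but the chosen 10 per group is recovered. It is a number for change within an arm. It contains no assumption about a difference between the doses.

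**2. Assumptions for the rest.** Normal data, common SD, 10 completers per arm, two-sided 5%, t-tests. An effect of 1 SD is used because the two inputs that give 10 per group are about that size: 44.5/44.3 = 1.00 and 1860/1835 = 1.01. Treating these within-person changes as effects over placebo is an assumption.

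**3. Two equally effective doses (1 SD each).** By simulation (40,000 trials), each placebo comparison has power 0.56, and exactly one of the two is significant in 0.33 of trials. It follows that:

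- both are significant in (0.56 + 0.56 − 0.33)/2 ≈ 0.40;
- neither is in 1 − 0.40 − 0.33 = 0.27.

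Independent comparisons would give 2 × 0.56 × 0.44 = 0.49; the shared placebo arm reduces this to 0.33. With no drop-out the figure is about 29-30% at 13 per arm and 26% at 15 per arm.

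**4. The direct dose contrast.** The 95% CI half-width for 10,000 minus 5,000 IU is t(0.975, 2n − 2) × SD × √(2/n). With n = 10 this is 2.101 × 0.447 = 0.94 SD. An observed difference of 0.5 SD would have an interval of about −0.44 to 1.44 SD. Power for a true 0.5 SD difference (a linear response reaching 1 SD at 10,000 IU) is about 18-19%. The smallest difference detectable with 80% power is about 1.32 SD.

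**5. Would an ordered test answer the question instead?** For equally spaced doses the linear contrast has weights (−1, 0, 1). The 5,000 IU mean drops out, leaving 10,000 IU minus placebo, which is already an endpoint. Its power at 10 per arm is 0.57 to 0.58 whether the true effects at 5,000 and 10,000 IU are (0, 1), (0.5, 1) or (1, 1) SD, so it cannot tell these dose patterns apart. Jonckheere-Terpstra is not the same test, but rejecting its null does not separate the two doses either.

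**The case against.** The strongest reply has four parts.

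- **Omission.** This is a journal article, and the exact contrasts may stand in a full protocol or analysis plan that is not shown. That would settle the matter if the article were silent. It is not silent: it fixes its endpoint contrasts against placebo and also claims to address the optimal dose. That mismatch is inside the document.
- **Exploratory aim.** The trial is labelled exploratory, its aims are mostly worded as immune effects of two doses, and optimal dose appears only in the Discussion. Estimating each dose against placebo is a recognised first step. This limits the weight of the point, but an exploratory label does not turn two placebo comparisons into a dose comparison.
- **Rank sum test.** A reader might infer that a comparison of the two doses is ruled out. The documents do not support that: the rank sum sentence names no arms, so such a test is possible. What can be said is that none is specified and no endpoint calls for one.
- **Significance patterns.** A reader might infer that the investigators intend to read a dose effect from which comparison is significant. No passage says so. The 33% is the error rate of a reading the plan leaves open, not of a stated rule.

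It is also tempting to argue that a trend test would gain power over the plan. It would not. The immunologic endpoints are not adjusted for multiplicity, and with effects of 0.5 and 1.0 SD the chance that at least one unadjusted placebo comparison is significant is 0.59, against 0.58 for the trend contrast. The price is a false-positive rate of about 9% instead of 5%. If both doses work equally, the trend contrast is the weaker one (0.58 against 0.73).

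**Conclusion.** The point holds as a mismatch between the stated question and the specified comparisons. The title, the design label and the Discussion promise information on dose; the endpoints and statistical section specify no contrast between the doses and no ordered-dose analysis.

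If the two placebo results are set side by side to judge dose, equally effective doses would show one significant and one non-significant result in about a third of trials. This rests on 10 completers per arm, 1 SD effects and normal data. Equal effects are plausible on the article's own terms: the Background proposes a serum level above 100 nmol/l for immune effects and gives the whole range of 5,000 to 10,000 IU/day as the means of reaching it.

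The comparisons with placebo are not invalidated by this point.

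**What to change.** - Within each cohort, pre-specify for each immunologic endpoint the 10,000-minus-5,000 IU difference in change from baseline, with its 95% CI, at weeks 16 and 24.
- Do not adjust this contrast for 25(OH)D achieved on treatment. Baseline adjustment can stay.
- State that no dose conclusion will rest on which placebo comparison is significant.
- Limit the optimal-dose claim in the Discussion to what the interval supports.
- An ordered test such as Jonckheere-Terpstra may be added as support, with a note that it does not separate the two doses. A linear (−1, 0, 1) contrast adds nothing of substance to 10,000 IU versus placebo.

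The cost is analysis wording and one extra estimate per endpoint and time point, with no new data. The drawback is precision: the half-width is about 0.94 SD at 10 per arm, and power for a 0.5 SD difference is about 18-19%. The plan should say so, so that a wide interval is not read as showing that the two doses are equivalent.
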